**Figure 2 figure2:**
[figure not shown]
Location of the acupoints.

### Health Education

We will introduce the basic concepts of KOA and the methods used to manage the associated risks to help participants protect their knees.

### MRI Data Acquisition

MRI will be performed at the MRI Center of The Third Affiliated Hospital of Henan University of Chinese Medicine. Resting-state fMRI will be performed at the beginning and end of the experiment. MRI data will be acquired using a 3.0-T magnetic resonance scanner (General Electric) with a 32-channel phase-array head coil. During the full scanning period, the participants will be asked to remain awake and motionless with their eyes closed.

Blood oxygen level independent resting-state functional images will be acquired using the following parameters: TR=2000 ms, TE=30 ms, flip angle=90°, 33 axial slices, and field of view (FOV) = 220 mm × 220 mm. T1-weighted images will be collected using the following parameters: 160 axial slices, TE=2.93 ms, flip angle=9°, TR=1900 ms, TE=30 ms, and FOV = 256 mm × 256 mm. T2-weighted images will be collected with the following parameters: 25 axial slices, TE=2.93 ms, flip angle=150°, TR=6300 ms, TE=86.0 ms, and FOV = 240 mm × 240 mm.

### Clinical Outcome Assessments

Validated pain detectors and questionnaires will be used to assess knee pain, psychological characteristics, and function at the beginning and end of the experiment. The clinical outcome assessments will be (1) the PPTs, (2) the NRS, (3) the Hamilton Depression Scale (HAMD), and (4) the Western Ontario and McMaster Universities Osteoarthritis Index (WOMAC). Additional outcome indices included the adverse events of treatment.

### Pressure Pain Thresholds

The PPT is a form of quantitative sensory testing that enhances the understanding of pain sensitivity and musculoskeletal pain [22-24]. Moreover, it has strong interrater reliability across multiple raters [25]. The PPT effectively depicts pain intensity and is widely applied in patients with KOA. PPTs will be measured using a portable machine (FDX50, Digital Force Gauge, Wagner Instruments) [26,27]. The patient will be placed in a supine position. The variable collector will select four points for measurement: (1) 3 cm medial to the midpoint of the medial patellar border, (2) the center of the patella, (3) 3 cm lateral to the midpoint of the lateral patellar border, and (4) the belly of the deltoid muscle of the affected upper limb (Figure 3) [28]. The pain test needle will be moved slowly at 0.1 kg/s until the participant feels pain. The measurement will be repeated 3 times at each site with an interval of 25 s, and the average will be calculated [29].

**Figure 3 figure3:**
[figure not shown]
Points used to measure the PPTs. PPT: pressure pain threshold.

### Numerical Rating Scale

The NRS is an elementary well-managed scale to assess pain intensity. Patients express the intensity of rest and movement pain using the numbers 0-10.

### Hamilton Depression Scale

The HAMD comprises 24 items, most of which are evaluated on a 5-point scale (0-4 points): 0=“none,” 1=“mild,” 2=“moderate,” 3=“serious,” and 4=“very serious.” A few items are assessed on a 3-point scale (0-2 points): 0=“none,” 1=“mild to moderate,” and 2=“serious.”

### Western Ontario and McMaster Universities Osteoarthritis Index

The WOMAC (0-10 cm) comprises 3 dimensions (ie, pain, stiffness, and joint function). The score ranges from 0 to 96, with higher scores indicating worse symptoms.

### Adverse Events of Treatment

All adverse events that may occur throughout the trial will be documented, including the time of occurrence, symptoms of discomfort, particular indications, severity, remedy supplied, time course of the action of amelioration, time of determination, and date of remedy termination.

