**Methods:**

This randomized controlled parallel trial will be conducted at the Tuina Clinic of the Third Affiliated Hospital of Henan University of Chinese Medicine (Zhengzhou, China). Patients with KOA will be randomly assigned (1:1) to 6 weeks of health education or Tuina. All patients in both groups will accept a resting-state functional magnetic resonance scan at the beginning and end of the experiment, and the resting-state functional connectivity and the voxel-based morphometry analysis will be performed to detect the RVM and PAG function and structure changes. The clinical outcome assessments will be (1) the pressure pain thresholds, (2) the Numerical Rating Scale, (3) the Hamilton Depression Scale (HAMD), and (4) the Western Ontario and McMaster Universities Osteoarthritis Index (WOMAC). Considering that this trial is a study of resting-state functional magnetic resonance imaging technology, resting-state functional connectivity and voxel-based morphometry are the primary outcomes, and clinical outcome assessments are secondary outcomes. Adverse events will be documented and assessed throughout. All main analyses will be carried out on the basis of the intention-to-treat principle. The outcome evaluators and data statisticians will be masked to the treatment group assignment to reduce the risk of bias.

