### Exit Criteria and Management

Exit criteria are as follows: (1) request by the participant and (2) intratreatment side effects.

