**Figure 1 figure1:**
[figure not shown]
Flowchart of the trial. fMRI: functional magnetic resonance imaging; HAMD: Hamilton Depression Scale; NRS: Numerical Rating Scale; PPT: pressure pain threshold; WOMAC: Western Ontario and McMaster Universities Osteoarthritis Index.

**Table 1 table1:** Chart of the trial’s time points.

Research process	Enrollment	Allocation	Beginning	End of the experiment
Eligibility screen	✓			
Demographic variables	✓			
Medical variables	✓			
Allocation		✓		
Consent			✓	
fMRI^a^ scan			✓	✓
PPTs^b^			✓	✓
NRS^c^			✓	✓
HAMD^d^			✓	✓
WOMAC^e^			✓	✓
Adverse events			✓	✓
Working practice record			✓	✓

^a^fMRI: functional magnetic resonance imaging.

^b^PPT: pressure pain threshold.

^c^NRS: Numerical Rating Scale.

^d^HAMD: Hamilton Depression Scale.

^e^WOMAC: Western Ontario and McMaster Universities Osteoarthritis Index.

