### Interventions

A panel of 2 clinical medical professionals with an academic background in Tuina and clinical medicine agreed to develop a standard protocol for Tuina and health education. The protocol’s feasibility will be examined to determine whether it is practicable and acceptable and to identify any realistic issues caused by the procedures. Given the nature of the treatment, participants will be informed that the trial will be without harm, compensation, and posttrial care.

Clinical medical professionals with ≥3 years of experience with Tuina will conduct the health education for the participants. Before the trial, clinicians will be trained to ensure standard procedures and compliance with treatment protocol. All participants in the Tuina group will receive three 20-minute sessions a week over a 6-week treatment course. The participants in the health education group will participate in health education sessions lasting 1 hour each (administered once weekly for 6 weeks). The participants are to maintain their dietary habits and regular physical activity throughout the study period. Throughout the trial, they will be informed that they are not permitted to entertain other remedies. To guarantee compliance, all participants are required to register for therapy in a written log.

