### Ethical Considerations

This trial was registered in the Chinese Clinical Trials Registry in 2023 (ChiCTR2300070289). The ethics committee of the Third Affiliated Hospital of Henan University of Chinese Medicine has approved this study protocol (ethics approval number 2022HL-031).

This RCT will adhere to the ethical principles governing biomedical research on human participants and respect fundamental human rights in accordance with international recommendations included in the Declaration of Helsinki and its subsequent revisions.

Participants will be given both written and oral information about why the trial will be conducted, its objectives, the potential risks associated, and the guidelines set out during the monitoring period. If a patient fulfills the inclusion criteria and agrees to enroll in the trial, they will provide written informed consent. Patients are free to withdraw consent and discontinue the trial at any time and for any reason.

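### Participants are to be told the trial is without harm, which contradicts the article's own risk, exit and adverse-event provisions; Table 1 also does not show the continuous adverse-event recording that the text promises

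*Protocol article*

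**What the plan says.** On recording, the Methods part of the Abstract states "Adverse events will be documented and assessed throughout". The section Adverse Events of Treatment states "All adverse events that may occur throughout the trial will be documented" and lists the details to be kept, including time of occurrence, severity, remedy and course. Clinical Outcome Assessments names adverse events as an additional outcome.

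Table 1 has four time columns: "Enrollment Allocation Beginning End of the experiment". The row "Adverse events" is ticked under the last two. No column covers the treatment weeks.

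On what participants are told, Interventions states "participants will be informed that the trial will be without harm, compensation, and posttrial care". Ethical Considerations says the written and oral information covers "the potential risks associated". Exit Criteria and Management gives "intratreatment side effects" as a reason for leaving the trial.

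On contact, Interventions states "All participants in the Tuina group will receive three 20-minute sessions a week over a 6-week treatment course". The education arm has one 1-hour session a week for the same six weeks.

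**The concern.** There are two inconsistencies and one risk that follows from the design.

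- **Participant information.** A trial that records the severity of harms and has an exit criterion for side effects cannot also tell participants that it is without harm. As written, the article gives two incompatible accounts of what participants hear about risk. An assurance of no harm could also make participants less ready to report events, although the article offers no evidence either way.
- **Schedule.** Adverse events carry the same two ticks as the outcomes measured once before and once after treatment. Staff working from the table could treat adverse events as another before-and-after item, leaving one enquiry after baseline and up to six weeks of recall. Dates of onset and the course of an event are hard to reconstruct over that interval. Data Management lets only outcome assessors enter data in the case report forms, and the table schedules their assessments at those two points, so this reading is not far-fetched.
- **Even-handedness.** The arms differ threefold in number of sessions. If events were picked up at sessions, the Tuina arm would have more occasions to mention them.

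What is at stake is the safety description and the participant information. The primary imaging outcomes are not affected.

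**Working it through.** The article gives no numerical safety target, so there is no figure to reproduce. The check is a comparison of sections, followed by simple counts.

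**Step 1: statements about harm.**

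| Section | What it implies |
|---|---|
| Interventions | Participants are told there is no harm |
| Ethical Considerations | Participants are told of potential risks |
| Exit Criteria and Management | Side effects during treatment can occur and lead to exit |
| Adverse Events of Treatment | Events can occur; severity and remedy are recorded |

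The first row is incompatible with the other three.

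**Step 2: statements about timing.** The Abstract and Adverse Events of Treatment both say that recording runs throughout. Table 1 shows the beginning and the end. The table has no treatment-period column and no row for the treatment sessions, so it cannot display anything between those points. It therefore fails to show continuous recording, but it does not exclude it.

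**Step 3: contacts, from Interventions.**

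- Tuina: 3 sessions × 6 weeks = 18 contacts; 18 × 20 min = 360 min.
- Education: 1 session × 6 weeks = 6 contacts; 6 × 60 min = 360 min.
- Ratio of contacts: 18 / 6 = 3. Total contact time is equal, and both arms are seen in each of the six weeks.

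**Step 4: could the contact ratio matter?** Suppose, as an assumption outside the documents, that a lasting complaint is recorded only at sessions, with the same chance q at each contact. The chance that it is recorded at least once is 1 − (1 − q)^n, where n is the number of contacts.

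| q (assumed) | Tuina, n = 18 | Education, n = 6 |
|---|---|---|
| 0.05 | 60% | 26% |
| 0.10 | 85% | 47% |
| 0.20 | 98% | 74% |
| 0.30 | 99.8% | 88% |
| 0.50 | about 100% | 98% |

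The gap runs from large to negligible according to q, which the article does not give. The model also leaves out the end assessment shared by both arms, and treats a 20-minute and a 60-minute contact as equally likely to bring out a report. The table shows that an imbalance is possible. It does not estimate one.

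**The case against.** The strongest reply concerns Table 1. A reader might infer from its ticks that adverse events are assessed only at the beginning and the end. The documents do not support that: the table has no column in between, two statements say recording is continuous, and the items to be recorded imply event-by-event documentation. Data Monitoring also says that safety is supervised throughout. This part of the reply stands, and what remains is a schedule that does not show what the text promises.

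A reader might also conclude that the safety comparison is both incomplete and unequal. Those conclusions need opposite readings. If the table governed, both arms would be asked at the same two points, which is sparse but equal. If the text governs, recording is not incomplete, and inequality arises only if events are collected at sessions, which the article nowhere says. How events are elicited is commonly left to a full protocol, and the article names no between-arm test of adverse events. This stands too, so the unequal number of sessions is a risk to guard against and not a demonstrated bias.

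On the harm statement, it can be argued that the sentence is an awkward list of things the trial does not provide, and that the consent form, which is not shown, may be correct. That limits the consequence: one cannot conclude that participants were misinformed. It does not rescue the sentence, which reports what participants will be told and conflicts with three other sections.

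**Conclusion.** The point holds in a limited form. The contradiction over harm is in the text, needs no assumption, and is the main part. The mismatch between Table 1 and the text is real but minor, and a column or footnote would settle it.

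The 18 and 6 sessions are correct counts, but any imbalance in reporting depends on two things the article does not state: whether events are collected at sessions, and how likely an event is to be recorded at each contact. Its size is unknown, and the illustrative percentages should not be cited as an estimate. The changes are worth making because they are cheap, remove a wrong statement from the account of participant information, and keep safety capture even-handed.

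**What to change.** 1. In Interventions, remove the statement that the trial is without harm, and align the participant information with the potential risks referred to in Ethical Considerations. Check the sentence against the exit criteria and the adverse-event section at the same time.
2. In Table 1, add the six-week treatment period to the adverse-event row, so that the schedule agrees with the Abstract and Adverse Events of Treatment.
3. Use the same scheduled enquiry once a week in both arms: at the weekly session in the education arm, at one fixed session of the three in the Tuina arm, and at the end assessment in both. List events volunteered at other sessions separately, so that any between-arm description rests on equal opportunities to report.

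The cost is a wording correction in the protocol and participant information, one question per week at contacts that already take place, and probably a few more mild events recorded. No new visits are needed.

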### Demographic or Medical Variables

The following demographic and medical variables will be collected for analysis: sex, age, marital status, occupation, ethnicity, education level, blood pressure, temperature, respiration, pulse, height, weight, body mass index, combination of disease and medication, K-L score, course of KOA, and history of major surgeries.

### Data Management

Clinical data will be carefully saved using printed and electronic case report forms (CRFs). Only outcome assessors will access the CRFs for data entry to guarantee data quality. CRFs will be verified for double entry and accuracy. During the trial, the Third Affiliated Hospital of the Henan University of Chinese Medicine will conduct regular visits (once a week) to review the conduct of the trial.

### Data Monitoring

The ethics committee will monitor for trial breaches and guarantee no conflicts of interest exist. Statisticians can obtain the last trial data set, which will exclusively accommodate coded data. The safety, advancement, and research integrity will be supervised throughout the research team conferences.

### Statistical Analysis

Prior to the analysis, a statistical program will be undertaken by a statistician. The program will embrace the processing approaches and the demanded data. Variables will be analyzed with IBM SPSS Statistics for Windows (version 25; IBM Corp).

### rsFC Analysis

For the ROI analysis, the ROI-to-ROI connectivity connections will be placed to a threshold by the intensity at the false discovery rate-corrected *P*<.05 (2-sided).

For the analysis of rsFC, we will use ROIs derived from the rsFC results. For the ROIs, we will use a threshold of voxel-wise *P*<.005 uncorrected and *P*<.05 corrected using Monte Carlo simulations with the 3dFWHMx and 3dClustSim applied [33].

### VBM Analysis

After completing these image analyses, we will obtain the GMV values of the key regions derived from rsFC for subsequent statistical analysis. The statistical significance between-group differences will be set at *P*<.05 with family-wise error correction.

### Data Analysis of Clinical Outcomes

#### Measurement Data

The Shapiro-Wilk test will foremost be conducted to confirm the normality of the uninterrupted data distribution. Independent sample *t* tests will be conducted for normally distributed data to evaluate the baseline characteristics. The Mann-Whitney U test will evaluate between-group differences for nonnormally distributed data.

#### Ranked Data and Count Data

The body mass index categorization, K-L score, NRS score, and WOMAC score are the rank data. Therefore, the Mann-Whitney U test will be applied for the between-group comparisons, and the Wilcoxon symbolic test will be applied for the intragroup comparisons. Count data will involve the ratio of the sex variable and knee constituent ratio, compared between the 2 groups via *χ*^2^ test of 4-fold table or Fisher test. Statistical significance will be set at *P*<.05 (2-sided).

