The pathogenesis of KOA is complex and involves heterogeneous factors in the central and peripheral nervous systems. However, peripheral candidate mechanisms are insufficient to explain widespread pain and the range of concomitant symptoms; thus, centrally driven mechanisms are deemed pivotal in the etiology of KOA. Our recent research demonstrated that the brain also participates in the pathophysiological changes in KOA and that central nervous system remodeling and function modifications may be among the central mechanisms associated with KOA [10]. Patients who reported higher levels of arthritic pain had greater opioid receptor availability in the periaqueductal gray (PAG), a key region of the descending pain inhibitory system, suggesting the alteration of this system in KOA [11]. Additionally, a functional magnetic resonance imaging (fMRI) trial demonstrated that the degree of PAG activation provides a sensitive and objective assessment of patellofemoral pain pressure in patients with KOA [12]. The descending pain inhibitory system originates in the PAG of the midbrain conduction duct and exerts its analgesic function through the relay of the rostral ventromedial medulla (RVM), inferior projection neuron of the cephalic medulla, and spinal-thalamic projection neurons in the superficial dorsal horn of the spinal cord [13]. Moreover, the subcortical structures and multiple cortices of the brain, comprising the anterior cingulate cortex, amygdala, insula, and hypothalamus, are also involved in pain modulation via the descending pain inhibitory system. The function of the descending pain inhibitory system in pain modulation and the management of the same have been substantially referenced [14,15].

We have, therefore, designed a single-center, parallel RCT to investigate the implications of Tuina and health education on KOA pain, resting-state functional connectivity (rsFC) of the cardinal regions of the descending pain inhibitory system (RVM and PAG), modifications of the voxel-based morphometry (VBM) of RVM and PAG, and behavioral alterations and their connections. We hypothesized that all treatments would relieve knee pain and share common pathways and that pain relief would be associated with the descending pain inhibitory system.

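### The between-group tests planned for the secondary clinical outcomes make no use of the baseline scores as a covariate, and the end-of-trial test for normally distributed PPT and HAMD is unclear

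*Protocol article*

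**What the plan says.** The clinical outcomes are PPT, NRS, HAMD and WOMAC. The Abstract makes them secondary to the imaging outcomes. Clinical Outcome Assessments gives their timing: "Validated pain detectors and questionnaires will be used to assess knee pain, psychological characteristics, and function at the beginning and end of the experiment". Table 1 shows all four at both time points.

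The analysis is split by data type.

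- **NRS and WOMAC** (Ranked Data and Count Data): "The body mass index categorization, K-L score, NRS score, and WOMAC score are the rank data". The next sentence assigns the tests: "Therefore, the Mann-Whitney U test will be applied for the between-group comparisons, and the Wilcoxon symbolic test will be applied for the intragroup comparisons". Significance is two-sided at 0.05.
- **PPT and HAMD** are not in that list, so they fall under Measurement Data. After a Shapiro-Wilk test, "Independent sample *t* tests will be conducted for normally distributed data to evaluate the baseline characteristics". Then: "The Mann-Whitney U test will evaluate between-group differences for nonnormally distributed data".

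Neither section names a baseline covariate, says whether Mann-Whitney is run on end values or on changes, or gives the within-group tests a descriptive role. The Introduction expects improvement in both arms: "We hypothesized that all treatments would relieve knee pain and share common pathways".

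**The concern.** Three things in this text are fixed badly or left unclear.

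1. Each participant's baseline score is collected, but no between-group comparison uses it as a covariate. In a trial of about 30 per arm, that gives up precision that costs nothing to obtain.
2. The text leaves two choices open that change the result. One is end value or change for NRS and WOMAC. The other is which test compares the arms at the end if PPT or HAMD is normally distributed. PPT is the variable used for the sample size.
3. Within-group Wilcoxon tests stand beside the between-group test at the same significance level, while the hypothesis is that both arms improve. A significant change in the Tuina arm is then expected whether or not Tuina adds anything to health education.

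**Working it through.** **Inputs from the Protocol article (Sample Size):** δ = 0.51 and σ = 1.36 for PPT, two-sided α = 0.05, and 29 per arm before dropout. The standardised effect is 0.51/1.36 = 0.375.

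**The plan's own figure.** 2 × (1.96 + 1.282)² × 1.36² / 0.51² = 149.5, that is 150 per arm for 90% power, not 29. The section also reports an SD of 2.62 for one group but calls 1.36 the larger SD. That is a separate defect. Here 29 per arm is simply taken as the planned size.

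**Assumption.** The correlation r between baseline and end score is not in the document, so r = 0.3, 0.5 and 0.7 are shown.

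**Variance left by ANCOVA, relative to the end score alone:** 1 − r².

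| r | 1 − r² | 29 per arm is worth | N per arm for 90% power |
|---|---|---|---|
| unadjusted | 1.00 | 29 | 150 |
| 0.3 | 0.91 | 29/0.91 = 32 | 136 |
| 0.5 | 0.75 | 29/0.75 = 39 | 113 |
| 0.7 | 0.51 | 29/0.51 = 57 | 77 |

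**Power by normal approximation:** Φ( δ / (σ√[(1 − r²) × 2/29]) − 1.96 ).

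- Unadjusted: 0.375/√(2/29) = 1.43, so Φ(−0.53) = 0.30.
- r = 0.3: 1.43/√0.91 = 1.50, giving 0.32.
- r = 0.5: 1.43/√0.75 = 1.65, giving 0.38.
- r = 0.7: 1.43/√0.51 = 2.00, giving 0.52.

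**Simulated power** (normal data, 29 per arm, true effect 0.375 SD):

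| Analysis | r = 0.3 | r = 0.5 | r = 0.7 |
|---|---|---|---|
| Mann-Whitney, end values | 25-27% | 25-27% | 25-27% |
| Mann-Whitney, change | 20% | 26% | 42% |
| ANCOVA | 30% | 35% | 49% |

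A repeat run agreed within about two percentage points, with the same ordering. At an assumed effect of 0.5 SD, which is not in the document, the ordering is also the same: ANCOVA 48%, 58% and 75%, end values 43-44%, change 32%, 45% and 66%.

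**Within-group tests.** Suppose there is no Tuina effect and both arms improve by 0.3 to 0.5 SD (assumed). The Wilcoxon test in the Tuina arm is then significant in 25% to 91% of simulated trials over r = 0.3 to 0.7. It is significant in the Tuina arm but not in the control arm in 8% to 26%. The between-group tests stay near 5%.

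**WOMAC format.** The outcome section says: "The WOMAC (0-10 cm) comprises 3 dimensions (ie, pain, stiffness, and joint function). The score ranges from 0 to 96". A simple sum of items scored 0-10 cannot have a maximum of 96, since 96/10 = 9.6 is not a whole number of items. If there are 24 items (an assumption), scoring 0-4 gives 24 × 4 = 96 and scoring 0-10 gives 24 × 10 = 240.

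**The case against.** The case for leaving the plan alone is substantial, and most of its limits stand.

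- **Validity.** With 1:1 randomisation the unadjusted between-group test keeps its type I error, and chance imbalance is already allowed for in the P value. A reader might infer bias. The documents do not support that, and the cost is precision.
- **Scope.** A reader might infer that every clinical outcome gets a rank test. That is certain only for NRS and WOMAC. For PPT and HAMD it depends on the normality test.
- **The t test.** A reader might infer that t tests are used only at baseline. That rests on one awkward sentence. An ordinary rule of t test if normal and Mann-Whitney if not is a plausible intention, so the fair statement is that the text is unclear.
- **Change scores.** Mann-Whitney might be run on change, which would use the baseline. At r = 0.7 this narrows the gap to ANCOVA from over 20 points to about 7. ANCOVA still had the highest power at every correlation tried.
- **Within-group tests.** A reader might infer that efficacy will be judged from them. Nothing in the article says so, and a between-group test is planned beside them. This is a risk of misreading, not a stated rule.
- **Rank methods.** They are defensible for a 0-10 scale, and a shift estimate can be given in scale units.
- **A later document.** The Statistical Analysis section promises a statistical programme before analysis, which could add covariates. But the article already names the tests, and as named they are unadjusted.

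**Conclusion.** The point holds as a low-cost improvement to secondary analyses, not as an error that invalidates them. The named between-group tests are valid but less precise than the collected data allow, and the text leaves open the end-of-trial test for normal data and the choice between end value and change.

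At 0.375 SD and 29 per arm, ANCOVA gains roughly 3 to 24 percentage points of power over Mann-Whitney on end values, and about 7 to 10 over Mann-Whitney on change. The size depends on the assumed correlation of 0.3 to 0.7 and on normal data. At r = 0.3 the gain over end values is small.

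A reader might infer that adjustment would make the trial adequately powered. It would not: 77 to 136 per arm would still be needed for 90% power over the same correlations, against 29 planned. The WOMAC contradiction is real but is a separate matter of measurement.

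**What to change.** - For PPT, NRS, HAMD and WOMAC, make the between-group analysis an ANCOVA of the end value on arm and the outcome's own baseline value. If ranks are preferred, use a rank-based or ordinal model with baseline as a covariate. Report the adjusted difference with its 95% CI. Naming one model per outcome also removes the uncertainty over the test for normal data.
- Keep Mann-Whitney as a sensitivity analysis and state whether it uses end values or changes.
- Label the within-group Wilcoxon tests descriptive, and state that conclusions about Tuina rest on the between-group comparison.
- Separately, state one WOMAC version, with its item range and total.

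The analysis changes are wording only. Every value needed is already in the assessment schedule. They should be dated and recorded before outcome data are examined by group. The WOMAC item needs only a check of the form in use.
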